### Outcomes

Primary endpoints are the number and stage of detected breast cancers, both DCIS and invasive, in each arm. Secondary endpoints are the false-positive results in the screening arms, and the sensitivity and positive predictive value of both screening strategies. Furthermore, cost-effectiveness and breast cancer mortality reduction of both strategies will be assessed. All analyzes will also be performed stratified for mammographic density.

A positive screening test is defined as a mammographic or MRI examination with a BI-RADS score of 0, 3, 4, or 5 and/or a clinical breast examination classified as ‘suspicious’. Interval cancers are defined as tumours diagnosed after a negative screening examination but before the next scheduled screening examination. Sensitivity is calculated as the number of screen-detected tumours divided by the total of screen-detected and interval tumours. The positive predictive value of a screening strategy is calculated as the proportion of women with a positive screening test, which after pathology indeed proved to be breast cancer.

Prospective assessment of mortality reduction requires a very lengthy follow-up and a large study population, which may not be feasible. To study this issue we will start with a less costly and time-consuming approach and estimate mortality reduction through a micro-simulation model: MISCAN, a well-validated micro-simulation model, originally developed to estimate the cost-effectiveness of the population-based screening program in the Netherlands
[38-40]. In the model, the natural history of breast cancer is modelled as a progression through 5 pre-clinical and invasive disease stages. At each pre-clinical stage, a tumour may either be clinically diagnosed or grow into the next pre-clinical stage. Screening may detect the tumour in a preclinical stage. Transition probabilities, stage durations and survival after clinical diagnosis or screen detection are based on data from the Dutch nation-wide screening program
[41,42]. The improvement of prognosis after detection by screening is based on the long-term effects of Swedish trials
[43-45]. A detailed description of the model has been published previously
[39].

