### Sample size/power calculation

Our primary aim is to detect a difference in tumour stage between the intervention and the current practice group. In the Dutch MRI Screening Study (MRISC) study, conducted from 1999 to 2007, over 1500 women with familial risk were included in the 6 participating centres
[11]. The incidence rate in this risk group was 7/1000 women years screened. Since the FaMRIsc study will have three more participating centres we intend to include 2000 women. We expect to detect about 50 breast cancers (both DCIS and invasive) in 4 years. With this number we are able to detect a difference in tumour size of 8 mm (SD tumour size: 9 mm) as statistically significant (two sided alpha =0.05) with a power of 80%. Eight mm is considered to be a clinically relevant difference.

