### Statistical methods

Primary outcome will be incidence and the difference in mean tumour size at diagnosis between the two arms. If normally distributed, this will be tested by means of the independent samples (unpaired) *t*-test. If not normally distributed, medians will be estimated and differences between distributions will be tested with the non-parametric Mann–Whitney *U* test.

Breast cancer incidence rates will be calculated as the total number of breast cancers detected per 1000 woman-years at risk. This will be calculated both including and excluding DCIS. Differences between these proportions will be compared using a chi-square test or Fisher’s exact test as appropriate.

All tests will also be performed stratified by mammographic density to examine the influence of density on the efficacy of MRI screening versus usual care. The influence of breast density on detection rates, tumour stage and false positive results in both arms will be analysed by means of analysis of variance (ANOVA).

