## Discussion

Twenty-five percent of all breast cancers occur before age 50 and especially familial breast cancer is seen at younger ages
[2]. A randomized controlled trial can provide the best evidence for any breast cancer mortality reduction attributable to digital mammography or MRI screening in this population.

Studies that offered MRI and mammography screening simultaneously have several shortcomings due to their paired design. Sensitivity of neither test without the other can be assessed. Nor the stage in which either test separately would have detected tumours.

With the results of our study we will be able to estimate the mortality reduction for screening women with familial risk with either digital mammography or additional MRI.

Furthermore, we will be able to assess whether mortality reduction by earlier detection differs with increasing breast density between screening with digital mammography or with additional MRI.

Breast density may be a key discriminator for choosing the optimal screening strategy below age 50 years for women with familial risk. If we can assess this, personalized cancer screening can be offered, based on a woman’s age, risk and breast density. This may optimize mortality reduction, whilst possibly decreasing over diagnosis. Compliance to screening will be best if there is convincing evidence that the most effective tool with the lowest side-effects is offered.

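### Repeating the between-arm tests within density strata does not test whether density changes the effect of MRI; one arm-by-density interaction term would

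*Protocol article*

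**What the plan says.** The influence of density is a stated aim in the Abstract. Three places in the article bear on how it will be analysed.

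- Outcomes: "All analyzes will also be performed stratified for mammographic density".
- Statistical methods: "All tests will also be performed stratified by mammographic density to examine the influence of density on the efficacy of MRI screening". The tests meant are those just described there: the unpaired t-test or Mann–Whitney test for tumour size, and the chi-square or Fisher test for incidence.
- Statistical methods, next sentence, which names ANOVA as the method: "The influence of breast density on detection rates, tumour stage and false positive results in both arms will be analysed by means of analysis of".

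The Discussion then looks ahead: "we will be able to assess whether mortality reduction by earlier detection differs with increasing breast density" between the two strategies, and it presents density as a possible basis for choosing between them.

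No section names an arm-by-density interaction or any other comparison of effects between strata. The number of strata and the cut-points are not given. Density itself is an automated measurement on the first digital mammogram of every participant (Interventions).

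**The concern.** The question is one of effect modification: is the difference between MRI and mammography larger at one density than at another? Stratum-wise testing gives a p-value for each stratum and none for the contrast between them. A significant result in dense breasts beside a non-significant one in non-dense breasts may reflect only that the strata are small or of unequal size. With about 50 cancers in the whole trial, each stratum has low power, so such a pattern is easy to obtain when the effect is the same everywhere.

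The ANOVA does not clearly close the gap. As worded it concerns the effect of density on outcomes within the arms. It could contain an interaction, but none is stated. Tumour size is not among its outcomes. It also suits poorly those it does list: detection and false positives are binary, and stage is ordinal.

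What is at stake is the density aim. The overall comparison of the arms is unaffected.

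**Working it through.** **Inputs from the article.** About 50 cancers, a difference of 8 mm, SD 9 mm, "two sided alpha =0.05", and "with a power of 80" percent (Sample size/power calculation); 1:1 allocation (Trial design); dense breasts in 50–74% of women aged 40–49 (Background).

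**Assumptions.** Two density strata; cancers equal in number in the two arms; cancers divided between strata from 50/50 to 74/26, which borrows the range for women as a range for cancers; t-tests on size.

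**The plan's own figure.** With 25 cancers per arm, SE = 9 × √(2/25) = 2.55 mm, and power = Φ(8/2.55 − 1.96) = 88% (87% by the noncentral t), not 80%. By the normal approximation 80% needs 20 per arm, and 25 per arm detect 7.1 mm. The stated figure is therefore conservative, and this does not affect the point.

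**Power within a stratum.** With n cancers per arm in the stratum, the noncentrality is 8 / (9 × √(2/n)) on 2n − 2 degrees of freedom.

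- 50/50 split: n = 12.5 in each stratum, noncentrality 8/3.6 = 2.22, power 56.7% in each.
- 74/26 split: n = 18.5 and 6.5, power 74.8% and 31.0%.

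**Chance that exactly one stratum is significant under the same true effect in both.** This is p1(1 − p2) + p2(1 − p1).

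| Common effect | 50/50 split | 74/26 split |
|---|---|---|
| 8 mm | 2 × 0.567 × 0.433 = 49% | 0.748 × 0.690 + 0.310 × 0.252 = 59% |
| 6 mm | 46% | 50% |
| 4 mm | 30% | 31% |
| none | 9.5% | 9.5% |

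A simulation of 40,000 trials with 12 cancers per arm per stratum and a common 8 mm effect gave 49% discordance. In the same runs an interaction test was falsely significant in 4.9%.

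**What an interaction test can detect.** SE = 9 × √(2/n1 + 2/n2), with n1 and n2 the cancers per arm in the two strata.

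| | 50/50 split | 74/26 split |
|---|---|---|
| SE | 5.09 mm | 5.80 mm |
| Power for an 8 mm interaction, Φ(8/SE − 1.96) | 35% | 28% |
| Detectable at 80% power, 2.80 × SE | 14.3 mm | 16.3 mm |
| Cancers for 80% power at 8 mm, 50 × (detectable/8)² | 159 | 207 |

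**The case against.** The strongest reply is that ANOVA over arm and density is an ordinary way to fit an interaction, and that a condensed article may leave the model terms to the full protocol or analysis plan. This stands in part: the article does have a second density analysis, and it may have been meant to include the interaction. But the sentence states no such term and leaves out tumour size. The article also expressly assigns the question of MRI efficacy by density to the stratified tests. That is a method fixed in the text, not a detail left open.

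Four other replies limit how far the point goes.

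- A reader might infer that a false density-specific recommendation is likely. The article sets no rule that turns discordant p-values into a recommendation, and elsewhere in the Discussion it says only that density may be a key discriminator. The 49% to 59% is the chance of a misleading pattern under a common 8 mm effect, and it falls with smaller effects.
- A reader might carry these figures over to the Discussion's statement on mortality. Under Outcomes, mortality reduction comes from the MISCAN micro-simulation, not from stratum t-tests on size. The figures do not measure the reliability of that estimate.
- The strata used here are assumed. Background says incidence rises with density, so the dense share of cancers could exceed the dense share of women.
- False-positive results come from repeated screens of 2000 women, not from about 50 cancers. The calculations do not speak to power for that outcome.

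**Conclusion.** The point holds. The method that the article assigns to the influence of density on MRI efficacy does not test it, and the adjacent ANOVA, as worded, does not supply the test. With two strata, equal cancers per arm and about 50 cancers in all, an identical effect in both strata would look different by significance in about 49% to 59% of trials at 8 mm and about 30% to 50% at 4 to 6 mm. A proper interaction test holds its false-positive rate near 5% but has only about 28% to 35% power for an 8 mm interaction. The trial can therefore estimate the modifying role of density on size, but imprecisely. The documents do not support saying that a wrong recommendation is likely, or that the modelled mortality result is unreliable to this degree. The matter should be corrected; it does not threaten the primary comparison.

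**What to change.** - Make one prespecified arm-by-density interaction term the basis for any conclusion about density, preferably with density continuous from the automated measurement.
- Fit it in a linear model for tumour size, and in models suited to the outcome for the rest: binary for detection and false positives, ordinal for stage. These would replace the ANOVA.
- Show stratum estimates with 95% confidence intervals, as description only.
- State the low power (about 28% to 35% for 8 mm; 14 to 16 mm detectable at 80%) and label size and stage results by density as exploratory.
- Qualify the density statement in the Discussion to match, noting that its mortality part rests on the MISCAN model.

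The cost is analysis wording and a softer claim. Density is already measured, and no new data, participants or procedures are needed. The drawback is that the interaction test will often be inconclusive, which the plan should say in advance.

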## Discussion

Twenty-five percent of all breast cancers occur before age 50 and especially familial breast cancer is seen at younger ages
[2]. A randomized controlled trial can provide the best evidence for any breast cancer mortality reduction attributable to digital mammography or MRI screening in this population.

Studies that offered MRI and mammography screening simultaneously have several shortcomings due to their paired design. Sensitivity of neither test without the other can be assessed. Nor the stage in which either test separately would have detected tumours.

With the results of our study we will be able to estimate the mortality reduction for screening women with familial risk with either digital mammography or additional MRI.

Furthermore, we will be able to assess whether mortality reduction by earlier detection differs with increasing breast density between screening with digital mammography or with additional MRI.

Breast density may be a key discriminator for choosing the optimal screening strategy below age 50 years for women with familial risk. If we can assess this, personalized cancer screening can be offered, based on a woman’s age, risk and breast density. This may optimize mortality reduction, whilst possibly decreasing over diagnosis. Compliance to screening will be best if there is convincing evidence that the most effective tool with the lowest side-effects is offered.

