**Methods/Design:**

This Dutch multicentre, randomized controlled trial, with balanced randomisation (1:1) has a parallel grouped design. Women with a cumulative lifetime risk for breast cancer due to their family history of ≥20%, aged 30–55 years are eligible. Identified BRCA1/2 mutation carriers or women with 50% risk of carrying a mutation are excluded. Group 1 receives yearly mammography and clinical breast examination (n = 1000), and group 2 yearly MRI and clinical breast examination, and mammography biennially (n = 1000).

Primary endpoints are the number and stage of the detected breast cancers in each arm. Secondary endpoints are the number of false-positive results in both screening arms. Furthermore, sensitivity and positive predictive value of both screening strategies will be assessed. Cost-effectiveness of both strategies will be assessed. Analyses will also be performed with mammographic density as stratification factor.

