**Discussion:**

Personalized breast cancer screening might optimize mortality reduction with less over diagnosis. Breast density may be a key discriminator for selecting the optimal screening strategy for women < 55 years with familial breast cancer risk; mammography or MRI. These issues are addressed in the FaMRIsc study including high risk women due to a familial predisposition.

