### Participants

Eligible participants are women aged 30–55 years with a cumulative lifetime risk (CLTR) of >20% because of a familial predisposition according to the modified tables of Claus
[1,27] or as assessed at a Clinical Genetics Centre. *BRCA1* and/or *BRCA2* mutation carriers or women with a 50% likelihood of such a mutation are excluded, since MRI screening is already advised for these women by the American Cancer Society (ACS), the American College of Radiologists (ACR), the United Kingdom’s NICE guideline and the European guideline of the European Society of breast imaging (EUSOBI)
[18,28-30]. Exclusion criteria are previous invasive cancer (potentially of influence on survival data), and a contraindication for contrast-enhanced MRI (decreased creatinin clearance, metal implants or claustrophobia).

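### The density analyses carry no age term, so the density effect, and any difference in MRI benefit between density strata, is partly an age effect

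*Protocol article*

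**What the plan says.** - **Population.** The Participants section states: "Eligible participants are women aged 30–55 years".
- **Density analysis.** Statistical methods states: "All tests will also be performed stratified by mammographic density to examine the influence of density on the efficacy of MRI screening versus usual care". It then names ANOVA as the tool for the influence of density on detection rates, tumour stage and false-positive results in both arms. Outcomes also commits to density stratification. Neither section mentions age as a covariate, stratum or interaction.
- **Density measurement.** Under Interventions, density is measured once, by an automated method on each participant's first digital mammogram.
- **Age, risk and density.** The Background lists age beside family history as a risk factor. It gives high or very high density in about 50–74% of women aged 40–49 and 20–44% of women in their 60s.
- **Intended use.** The Discussion says "Breast density may be a key discriminator for choosing the optimal screening strategy below age 50 years for women with familial risk" and, if this can be assessed, that "personalized cancer screening can be offered, based on a woman’s age, risk and breast density". The parallel sentence in the abstract refers to "selecting the optimal screening strategy for women < 55 years with familial breast cancer risk".

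**The concern.** Density is not randomised. Women with dense and non-dense breasts differ in age, and by the article's own account age is related to both cancer risk and density. A difference in detection rate, stage or false positives between density groups therefore mixes two influences. The same applies to the contrast that matters most here, whether MRI gains more over mammography in dense breasts. If the gain varies with age for any reason, an analysis by density alone credits part of that variation to density.

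This matters because the Discussion wants age and density as separate inputs to a choice of screening method. An analysis that never puts them in the same model cannot say how much each contributes. A woman of 35 and a woman of 55 with the same density would be given the same estimate.

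**Working it through.** **1. Inputs.** From the article: entry age 30–55; 2000 women; 7 cancers per 1000 woman-years; about 50 cancers in 4 years; tumour-size difference 8 mm, SD 9 mm, two-sided alpha 0.05; the density percentages above. Not in the article: the entry-age distribution, follow-up per woman, density at ages 50–59, and the share of cancers below 50. These are treated as assumptions.

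**2. The plan's own count.** 2000 × 4 × 7/1000 = 56 cancers, against the stated figure of about 50. Fifty cancers correspond to 50/0.007/2000 = 3.57 years per woman. Four years is thus the study period for the count, not a stated follow-up per woman, so 2 and 4 years are both tried below.

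**3. Woman-years at age 50 or over.** Assume uniform entry from 30 to T and follow-up of F years. Women entering at 50 or over contribute all their time, and those entering in the F years before 50 contribute half on average:

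share = (T − 50)/(T − 30) + ½ × F/(T − 30)

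| T | F | Share at 50 or over |
|---|---|---|
| 55 | 2 | 5/25 + 1/25 = 24% |
| 55 | 4 | 5/25 + 2/25 = 28% |
| 56 (up to the 56th birthday) | 2 | 6/26 + 1/26 = 27% |
| 56 | 4 | 6/26 + 2/26 = 31% |

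**4. Age mix of the density strata (illustration).** Take 20% entering at 50 or over (5/25). Apply the 40–49 density figure to everyone below 50, and for ages 50–59 take the midpoint between the 40–49 and 60s figures.

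- Middle of both ranges: 62% dense below 50; (62 + 32)/2 = 47% at 50 or over. Low-density stratum: 0.20 × 0.53/(0.20 × 0.53 + 0.80 × 0.38) = 0.106/0.410 = 26% aged 50 or over. High-density stratum: 0.20 × 0.47/(0.20 × 0.47 + 0.80 × 0.62) = 0.094/0.590 = 16%.
- Steepest fall (74% to 20%, midpoint 47%): 0.106/0.314 = 34% against 0.094/0.686 = 14%.
- Flattest fall (50% to 44%, midpoint 47%): 0.106/0.506 = 21% against 0.094/0.494 = 19%.

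The imbalance runs in one direction throughout, but its size ranges from 2 to 20 percentage points.

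**5. What randomisation covers.** Allocation is 1:1, so within a density stratum age does not differ systematically between the arms. Two quantities remain exposed: the effect of density itself (the ANOVA), and the difference between strata in the arm effect. For the second, a main effect of age is not enough. If the arm effect varies with age, an arm-by-age term is needed beside arm-by-density.

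**6. Cost in precision.** Take a tumour-size model on 50 cancers with an intercept, arm, one density term and their interaction. It leaves 46 residual degrees of freedom; adding age and arm-by-age leaves 44. Restricting to cancers below 50 costs far more. With equal arms and a t-test at 8 mm, 50 cancers give 87% power (above the stated 80%), 40 give 78%, 30 give 65% and 20 give 47%, all before any split by density.

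**The case against.** **An analysis plan not shown may add age.** That is possible, and if so the point is already met. But the article is not silent here. It names the method for the density question, and the method as named has no age term.

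**Density can serve as a marker without being separated from age.** This is true if density alone is to decide the screening method. It stands as a limit on the point. It does not meet the Discussion's wish to use age and density together.

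**Age does enter the micro-simulation model.** Under Outcomes, entry-age distribution is an input and age at diagnosis a calibration target. That covers the modelled mortality and cost results. It does not adjust the ANOVA or the stratified tests, and density is not among the inputs listed there.

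**The density figures are for women in their 60s, who are largely outside the trial.** This is fair: the article gives nothing for ages 50–59, so the size of the imbalance is unknown.

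**Stronger readings a reader might infer.**
- That the trial will issue a conclusion for women under 50 which rests on women outside that age. The documents do not support this: the sentence says only that density may discriminate, the next one is conditional, and no analysis population is defined by it.
- That the abstract's upper limit of 55 is a comparable mismatch. It nearly matches eligibility. On the same uniform-entry assumption with 4 years of follow-up, only 8% (½ × 4/25) to 12% (1/26 + ½ × 4/26) of woman-years fall at 55 or over.
- That the randomised comparison within a stratum is biased by age. It is not.

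**Conclusion.** The point holds in a limited form. As described, the density analyses cannot separate density from age, and the article's own Background supplies the reason to expect the two to be mixed. The direction is clear: the low-density group will be older. The amount is not known. The figure of 24–31% of woman-years at age 50 or over depends on uniform entry ages and 2–4 years per woman, and the stratum age mix in the illustration depends further on an interpolated density for ages 50–59. These figures describe exposure and composition; none of them measures bias in an estimate. No error in the sample size, the primary comparison or eligibility follows from this. It is a worthwhile, inexpensive improvement to a stated secondary analysis.

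**What to change.** In Statistical methods, state that the analyses of density (the ANOVA or an equivalent regression, and the arm-by-density comparison) include age at entry as a continuous covariate, and that an arm-by-age term is fitted alongside arm-by-density where the number of cancers allows. Show results below 50 and at 50 or over descriptively. Do not restrict the density conclusion to cancers below 50: with about 50 cancers in all, that would leave too few.

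Cost: one or two extra parameters and some loss of precision, including what the correlation between age and density takes away. No new data are needed, since age is required for eligibility and for the simulation model. With so few cancers the arm-by-age and arm-by-density terms will be imprecise and should be reported with intervals.

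As an editorial matter, use one age range in the density sentences of the abstract and the Discussion.
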